## **3.3 Study protocol**

The study will be performed in the Hanusch Hospital and the connected health centres of the ÖGK, Vienna.

### **3.3.1 Study Visits**

After baseline examination (prior to cataract extraction) three postoperative follow up visits will be scheduled (one week, one month, three month). Occurrence of dry eye signs and symptoms will be evaluated during each study visit.

#### **3.3.1.1 Study schedule**

- Visit 1 - Screening
- Visit 2 - Baseline (prior to cataract surgery, within 30 days after screening)
- Visit 3 - Follow up 1 – (7±1 days after cataract surgery)
- Visit 4 - Follow up 2 – (30±7 days after cataract surgery)
- Visit 5 - Follow up 3 – (90±7 days after cataract surgery)

#### **3.3.1.2 Dry eye related examination**

Dry eye related examination will be performed during baseline visit and during all follow ups by a masked investigator.

Dry eye related examinations include all of the following

- Ocular surface disease index (OSDI) score
- Photograph of the anterior segment
- Meibomian gland expressibility
- Fluorescein Staining / Lissamin green staining grading using the modified Oxford Scale
- Break Up Time (BUT)
  - Fluorescein BUT
  - Non-invasive BUT

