#### **3.2.1 Number of subjects**

For sample size calculation we used the data published earlier by Villani et al.[1] In the study 50% of the patients with an OSFI score higher than 0.3 (high risk group) developed dry during the study period. The rate was 9.6% in the group with an OSFI score lower than 0.3. These two proportions were used to calculate the sample size. We assume a clinical benefit of the lubrication drops if the rate of occurrence of dry eye in the high-risk group is reduced close to the value of the low-risk group (15%).

Using an alpha error of 0.05 and a power of 80 % we need to include 27 in group 1 and group 2. Due to the long study period, we expect a dropout rate of 30%. Therefore, we need to include 39 patients in group 1 and group 2. 39 patients will be included in group 3.

In total 117 patients will be enrolled into the study.

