### **3.3.1.5 Withdrawal and replacement of subjects**

Subjects must be withdrawn under the following circumstances:

- at their own request
- use of forbidden medication
- development of an Exclusion Criterion during study participation

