## **3.4 Variables and biometric methods**

### **3.4.1 Outcome variables**

**Primary Endpoint:** Rate of dry eye symptoms defined by OSDI  $\geq 13$  at 3 months

**Secondary Endpoints:** Rate of DED defined by OSDI  $\geq 13$  plus at least one of the following:

Presence of ocular surface staining, TFBUT  $< 10$ s at 1 week, 1 and 3 months

Comparison of dry eye related parameters between the groups: TFBUT, Staining scores (modified Oxford Grading Scale) at 1 week, 1 and 3 months

Change of dry eye related parameters during the study period (baseline, 1 week, 1 and 3 months) in the study eye: TFBUT, Staining scores (modified Oxford Grading Scale)

Change of OSDI score during the study period (baseline, 1 week, and 3 months)

**Exploratory Endpoints:** Comparison of dry eye symptoms rate DED rate between Group 1, Group 2 and Group 3, BCVA, IOP, Concomitant medication and Adverse Events

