### **4.2 Ocular surface disease index – OSDI**

The OSDI Questionnaire is a standardized questionnaire to evaluate the subjective disease burden caused by dry eye syndrome. The patients answer up to 12 questions regarding their symptoms. Thereafter, the OSDI Score is calculated.

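### The 3-month OSDI has no collection route outside the clinic visits, so the expected 30% dropout leaves the primary comparison open to bias that enrolling 39 per arm does not address

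*Protocol*

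**What the plan says.** All references are to the protocol.

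- **Endpoint (3.4.1).** "Rate of dry eye symptoms defined by OSDI" at or above 13, at 3 months.
- **Instrument (4.2).** The OSDI is a questionnaire: "The patients answer up to 12 questions regarding their symptoms". It needs no dye, slit lamp or device.
- **Collection (3.3.1.2).** The OSDI heads the list of dry eye examinations, and "Dry eye related examination will be performed during baseline visit and during all follow ups by a masked investigator". Section 3.3.1 and the schedule in section 5 also place it at the study visits. Visit 5 is at day 90 ± 7 after surgery. No phone, post or online route is described.
- **Withdrawal (3.3.1.5).** "Subjects must be withdrawn under the following circumstances": the patient's own request, use of forbidden medication, or a newly arising exclusion criterion. The section does not mention collecting outcomes afterwards.
- **Expected loss (3.2.1).** "Due to the long study period, we expect a dropout rate of 30" per cent. The response is to enrol 39 instead of 27 in each randomised arm.
- **Missing data (3.4.2.2).** Observations with missing data are left out of the analysis.

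**The concern.** Read together, these sections leave a patient who misses Visit 5, or who is withdrawn before it, without a primary outcome and outside the primary comparison. At the protocol's own dropout figure that is nearly a third of each randomised arm.

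The loss may not be random. Section 3.3.1.4 asks patients to use no eye drops beyond their assigned routine, and 3.3.1.5 withdraws users of forbidden medication. A Group 1 patient with troublesome dryness who turns to lubricant drops could therefore leave the data because of the symptom being counted, and this could happen more often in one arm than in the other. The protocol does not say how often this is expected.

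This is a matter for the protocol. A statistical analysis plan can choose how to handle a missing answer, but it cannot recover one that was never requested.

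**Working it through.** **Inputs.** From 3.2.1: rate in Group 1 p₁ = 0.50, rate in Group 2 p₂ = 0.15, alpha 0.05, power 80%, 27 per arm evaluable, 30% dropout, 39 per arm enrolled. Sidedness is not stated. Two-sided is assumed because it reproduces 27 with the ordinary uncorrected formula; a one-sided test with continuity correction also gives 27.

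**Step 1: reproduce the plan's figures.** With pooled variance and p̄ = 0.325,

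n = [1.960·√(2·0.325·0.675) + 0.8416·√(0.50·0.50 + 0.15·0.85)]² / 0.35² = (1.298 + 0.517)² / 0.1225 = 26.9, so 27 per arm.

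Inflation: 27 / (1 − 0.30) = 38.6, so 39. Both figures are reproduced and the inflation is done correctly.

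**Step 2: patients without a primary outcome.** 39 × 0.30 = 11.7, about 12 per arm. The remaining 39 × 0.70 = 27.3 per arm give 80.6% power by the normal approximation, so the planned power is met.

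**Step 3: how far the missing answers could move the result.** If a fraction m is missing and the observed rate is p, the rate among all randomised lies between p(1 − m), when no missing patient has symptoms, and p(1 − m) + m, when all do.

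| Missing per arm | Group 1 | Group 2 | Difference, Group 1 − Group 2 |
|---|---|---|---|
| 30% | 35.0% to 65.0% | 10.5% to 40.5% | 35.0 − 40.5 = −5.5 to 65.0 − 10.5 = +54.5 points |
| 10% | 45.0% to 55.0% | 13.5% to 23.5% | 45.0 − 23.5 = +21.5 to 55.0 − 13.5 = +41.5 points |

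At 30% missing, even the full planned effect of 35 points would not fix the sign of the difference. At 10% it would. These are worst-case limits that ignore sampling error. The 10% is an illustration and does not come from the protocol.

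**Step 4: power, as a best case.** Exact enumeration of two binomials, uncorrected two-sided chi-square test at 5%, assuming that recovered patients have the same rates as completers:

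| Evaluable per arm | 50% v 15% | 50% v 20% |
|---|---|---|
| 27 (30% lost) | 82% | 66% |
| 33 (half the losses recovered) | 89% | 75% |
| 35 (10% lost) | 90% | 77% |
| 39 (nobody lost) | 93% | 81% |

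**Step 5: what if recovered patients differ.** Suppose 6 patients are recovered in each arm, and the 6 in Group 2 have stopped the drops and have a 50% rate. The Group 2 rate becomes (27·0.15 + 6·0.50) / 33 = 7.05 / 33 = 21.4%. Exact power with 33 per arm is then about 71%, below the 82% with 27 completers.

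**The case against.** The strongest counter-case has five parts.

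- **Cause of the loss.** A reader might infer that the plan gives up 30% of its patients because it collects the OSDI only in clinic. The protocol does not say so: 3.2.1 attributes the figure to the length of the study. It is a planning allowance for dropout, and no passage forbids a remote form. This stands, and the causal claim should not be made.
- **Sample size.** A reader might infer that the trial is underpowered. It is not, by its own assumptions: "Using an alpha error of 0.05 and a power of 80 % we need to include 27 in group 1 and group 2" is reproduced and 39 already covers the loss. This stands.
- **Size of the remedy.** A reader might infer that remote collection would supply all 12 missing answers per arm and lift power to 93%. The documents do not split the 30% into missed visits, own requests and mandatory withdrawals. Someone who leaves at their own request may not answer a call, and someone who withdraws consent must not be called. Step 5 shows that power could even fall. This stands; the power figures are a ceiling.
- **Visits are needed anyway.** The secondary endpoint of dry eye disease requires staining or break-up time, and safety measures are taken at each visit. This is true, but it does not count against a fallback for the primary endpoint alone.
- **Ordinary practice.** Taking the OSDI with the examination is normal in a single-centre study, and the quoted sentence in 3.3.1.2 contains no error. This is also true. The weakness lies in the combination of sections and in the absence of a second route.

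The exposure to bias survives. Extra enrolment replaces numbers but does not replace the patients who left. Nor is it enough that remote contact is not prohibited: calls made without a stated route, window and masked caller would be unplanned and could differ between arms.

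**Conclusion.** The point holds as an inexpensive improvement that rests on bias, not on power. Following the protocol as written, about 12 of 39 patients per arm may have no primary outcome. In the worst case the difference among all randomised patients then ranges from −5.5 to +54.5 points around an observed 35, against +21.5 to +41.5 if the loss were held to 10%.

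This assumes that the expected 30% occurs equally in both arms, that the observed rates equal the planning rates of 50% and 15%, and that some of those lost would still answer a short form. The last assumption cannot be checked from the documents. The limits show what the missing data leave open; they do not predict that such a bias will occur. The sample size calculation needs no correction.

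**What to change.** In 3.3.1.1, 3.3.1.2 and 3.3.1.5, state that:

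- the 3-month OSDI is requested by phone, post or online form, within day 90 ± 7, from every randomised patient who does not attend Visit 5 or has been withdrawn, unless consent is withdrawn;
- any caller is masked to the arm, and the mode of collection is recorded;
- enrolment stays at 39 per arm;
- the primary analysis is repeated without the remote answers as a check.

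No treatment, rescue or withdrawal rule has to change; withdrawn patients are only asked for the questionnaire.

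**Cost.** A short protocol wording change and at most about 12 contacts per arm. A minority of forms will come from a different mode, which the repeated analysis addresses. Clinic visits remain necessary for the dry eye disease endpoint and the safety measures, and the remote form supports only the symptom endpoint.

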**3.3.1.3 Safety parameters**

In addition to the dry eye related examination visual acuity, intraocular pressure measurements and slitlamp biomicroscopy are performed during each study visit.

**3.3.1.4 Randomization**

The eye scheduled for cataract surgery will be selected as the study eye. Patients included into the study are allocated to one out of three groups. Patients with an OSFI score equal or higher than 0.3 (high risk) will be randomized into group 1 or 2, using an online randomisation tool (<https://randomizer.org>, list randomizer) by an unmasked member of the study staff.

**Group 1** receives the routine postoperative treatment (*Yellox eye drops* bid for four weeks after surgery, Bausch and Lomb, Germany), serves as the **standard of care group**.

**Group 2** is the treatment group and will receive *Systane Hydration MDPF eye drops* (Alcon, USA) in both eyes four times a day starting after surgery until the three-month visit in addition to the routine treatment (*Yellox eye drops* bid for four weeks after surgery, Bausch and Lomb, Germany). Allocation to group 1 and group 2 will be randomized. All patients will receive a log to document the use of eye drops. Group 2 serves as the **treatment group**.

Patients with OSFI score below 0.3 (low risk) will be included in **group 3** and serve as a **reference group**. All patients are asked not to use any other eye drops other than their routine therapy (*Yellox eye drops* bid for four weeks after surgery, Bausch and Lomb, Germany). In case of significant complaints due to dry eye a rescue medication will be offered to the patient.

**Group 1 (Standard of care):** OSFI higher or equal 0.3, *Yellox eye drops* twice a day for 4 weeks

**Group 2 (Treatment):** OSFI higher or equal 0.3, *Yellox eye drops* twice a day

for 4 weeks and *Systane Hydration MDPF* eye drops 4 times a day for the whole study period (3 month)

**Group 3 (Reference):** OSFI lower 0.3, *Yellox eye drops* twice a day for 4 weeks

### **3.3.1.5 Withdrawal and replacement of subjects**

Subjects must be withdrawn under the following circumstances:

- at their own request
- use of forbidden medication
- development of an Exclusion Criterion during study participation

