#### **3.2.3 Inclusion criteria**

- Age older than 18 years
- Cataract surgery scheduled in one or both eyes
- Scheduled for monofocal or monofocal-toric IOL implantation
- OSDI lower than 14
- OSFI higher or equal to 0.3 – *Group 1 and Group 2*
- OSFI lower than 0.3 – *Group 3*

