### **3.2.4 Exclusion criteria**

- Presence of dry eye symptoms preoperatively
- Occurrence of complications during surgery
- Usage of systemic antibiotic therapy
- Any pathology of the ocular surface except dry eye disease (e.g. corneal scarring, cornea ectasia)
- Ocular surgery within prior 3 months
- Ocular injury within prior 3 months
- Ocular herpes of eye or eyelid within prior 3 months
- Active ocular infection
- Active ocular inflammation or history of chronic, recurrent ocular inflammation within prior 3 months
- Eyelid abnormalities that affect lid function
- Ocular surface abnormality that may compromise corneal integrity
- Pregnancy

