#### **3.4.2.3 Biometric methods - Adverse events/Safety investigations**

All adverse events will be properly listed, and an appropriate method will be used to summarise the data. Visual acuity, intraocular pressure and anterior segment findings (such as inflammatory reactions) are documented during each study visit.

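### The mandatory withdrawal rule conflicts with admitting patients scheduled for surgery in both eyes: a second-eye operation before Visit 5 compels withdrawal and loses the month-3 primary outcome

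*Protocol*

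**What the plan says.** Three sections of the protocol meet on this point.

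- **Inclusion (3.2.3)** admits patients with "Cataract surgery scheduled in one or both eyes". Nothing says when a second eye may be operated on relative to the study visits.
- **Exclusion (3.2.4)** lists "Ocular surgery within prior 3 months" and "Active ocular inflammation or history of chronic, recurrent ocular inflammation within prior 3 months". Neither item is limited to the study eye or to the time before enrolment, and neither exempts the study operation.
- **Withdrawal (3.3.1.5)** opens with "Subjects must be withdrawn under the following circumstances" and gives as its third trigger "development of an Exclusion Criterion during study participation". No criterion is exempted. The section heading mentions replacement, but the text gives no replacement rule.

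Related provisions:

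- The Schedule of Events (section 5) puts randomisation at Visit 1 and cataract surgery at Visit 2. Visit 5, which carries the primary endpoint, falls 90±7 days after surgery.
- Section 3.3.1.4 states: "The eye scheduled for cataract surgery will be selected as the study eye".
- Section 3.4.2.2 leaves missing observations out of the analysis.
- Section 3.4.2.3 says that "anterior segment findings (such as inflammatory reactions) are documented during each study visit".

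**The concern.** The inclusion criteria invite patients whom the withdrawal rule may later remove. Someone scheduled for both eyes still has an operation to come after the index one, unless both are done in one session, which the protocol does not mention. If it takes place before Visit 5, the patient has developed a listed exclusion criterion and withdrawal is compulsory. Nothing requires the second operation to wait.

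The patient has been randomised by then, and the primary comparison is the rate of OSDI ≥13 at month 3 in Group 1 versus Group 2. With no follow-up after withdrawal described, the month-3 questionnaire would not be collected and the patient would leave that comparison as a missing observation. The rule thus turns a foreseeable clinical event into lost primary data. The 30% dropout allowance in 3.2.1 is justified by the length of the study, not by second-eye surgery.

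If staff set the rule aside, the protocol still has a gap. With both eyes scheduled, the sentence in 3.3.1.4 does not single out one study eye, yet changes in TFBUT and staining are study-eye endpoints. The month-3 OSDI, a patient-level score, would also come from some patients operated on again more recently than 90 days before.

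**Working it through.** **Step 1. The sections side by side.** Take a randomised patient with both eyes scheduled, operated on at Visit 2 (day 0), whose second eye is operated on at day t.

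- 3.2.3: eligible.
- 3.2.4: from day t the patient has had ocular surgery in the preceding 3 months.
- 3.3.1.5: an exclusion criterion has developed during participation, so withdrawal is compulsory.
- If t falls before Visit 5 (day 83 to 97), withdrawal precedes the primary assessment.
- 3.4.2.2: the absent month-3 value is left out.

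If t falls after Visit 5, nothing is lost. The rule therefore reaches patients with second-eye surgery during follow-up, not all bilateral patients.

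**Step 2. Reproducing the stated sample size.** Inputs from 3.2.1: p1 = 0.50, p2 = 0.15, alpha 0.05, power 80%. Sidedness is not stated; two-sided is assumed. With p = (0.50 + 0.15)/2 = 0.325 and no continuity correction:

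n = [1.96·√(2·0.325·0.675) + 0.842·√(0.50·0.50 + 0.15·0.85)]² / 0.35²

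= [1.96·0.662 + 0.842·0.614]² / 0.1225 ≈ 26.9, so 27 per group.

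Inflation: 27/(1 − 0.30) = 38.6, so 39. Both stated figures reproduce, and power at 27 per group is 80.2%.

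**Step 3. Room in the plan.** 39 − 27 = 12 patients per arm, or 31%, can be lost for all reasons together before the arm falls below the required 27.

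**Step 4. Effect of second-eye withdrawals.** Let w be the share of patients per arm withdrawn for second-eye surgery before Visit 5. The protocol gives no value, so w is an assumption shown over a range. Power = Φ{[0.35·√n − 1.96·0.662]/0.614}.

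| w (assumed) | Only losses: n = 39(1 − w) | Power | On top of 30% dropout: n = 39·0.70·(1 − w) | Power |
|---|---|---|---|---|
| 0 | 39 | 93% | 27.3 | 81% |
| 10% | 35.1 | 90% | 24.6 | 76% |
| 20% | 31.2 | 86% | 21.8 | 71% |
| 30% | 27.3 | 81% | 19.1 | 65% |
| 50% | 19.5 | 66% | 13.7 | 50% |

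The two sets of columns bracket the possibilities: the 30% allowance either absorbs these withdrawals entirely or not at all.

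**Step 5. Which criteria operate after randomisation?** Intraoperative complications are on the exclusion list and can arise only at Visit 2, after randomisation at Visit 1. The list is therefore not purely an entry list. Preoperative dry eye symptoms, by contrast, are expressly tied to the time before surgery. The surgery and inflammation items carry no such limit, so the reader has to guess.

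**The case against.** The strongest reply is that the surgery criterion looks back from the eligibility check, which the Schedule of Events places at Visit 1 only, and that no site would withdraw a patient for having the operation under study. For the index operation this stands. A reader might infer from the wording that every patient must be withdrawn, since the index operation itself meets the criterion at Visit 3. The documents do not support that as intended practice: surgery is a scheduled procedure and inflammatory reactions are recorded at follow-up. The missing exemption is a drafting flaw. The reply does not settle second-eye surgery, because 3.3.1.5 expressly extends the exclusion list beyond entry and nothing marks a second operation as a study procedure.

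A reader might also infer that all patients with both eyes scheduled are lost. That does not follow: only second operations before Visit 5 count, and neither their timing nor the bilateral share is given. Every value of w above is therefore an assumption, and at 10% with few other losses the allowance suffices.

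A third inference would be that the rule removes patients for reaching the outcome. OSDI ≥13 after surgery triggers nothing: the symptom criterion is limited to the preoperative period, and the ocular-surface pathology criterion exempts dry eye disease. The separate item "Ocular surface abnormality that may compromise corneal integrity" has no such exemption and could catch an occasional severe case, but the protocol does not equate it with the endpoint.

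Two further points stand. Section 3.4.2.2 speaks of missing data, not of withdrawn patients, so loss of the month-3 value is an inference from the absence of any post-withdrawal follow-up. And if second-eye surgery is equally frequent in Groups 1 and 2, as randomisation would lead one to expect, the main harm is lost precision rather than bias. How second-eye surgery is handled in the analysis may be set out in a statistical analysis plan not shown here, so its absence from the protocol is not held against it.

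**Conclusion.** The conflict between 3.2.3, 3.2.4 and 3.3.1.5 is real and should be fixed. Followed as written, the protocol withdraws randomised patients whose second eye is operated on before Visit 5, and their month-3 primary outcome is lost. The size cannot be fixed from the document. A small share, absorbed within the dropout allowance, costs nothing against the planned 80% power; a 20% share on top of 30% other losses brings power to about 71%. These figures rest on the protocol's rates of 50% and 15%, a two-sided test without continuity correction, equal loss in both arms and no outcome collection after withdrawal. The missing exemptions for the index operation and postoperative inflammation, and the undefined study eye in bilateral cases, are lesser matters of wording. The study-eye point touches the eye-level secondary endpoints, not the patient-level primary one.

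**What to change.** 1. Reconcile 3.2.3, 3.2.4 and 3.3.1.5. State which exclusion criteria operate after randomisation, including intraoperative complications, and how the index operation, postoperative inflammation and second-eye surgery are treated. A blanket statement that the criteria apply only up to randomisation would not do, since it would void the intraoperative-complication item. Which events end study treatment remains a clinical matter for the sponsor and the investigator.
2. Separate treatment from follow-up. State that meeting such a criterion after randomisation does not by itself end outcome collection or remove the patient from the primary Group 1 versus Group 2 analysis, unless the patient withdraws consent.
3. In 3.3.1.4, define the study eye as the eye operated on at Visit 2.
4. Record the date of any second-eye surgery on the case report form, so that its influence on month-3 OSDI can be examined.

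The cost is protocol wording and one date field, with no additional patients, visits or procedures. The downside is some extra variability in month-3 OSDI from patients with a recent second operation.
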